## Introduction

### Background and rationale {6a}

Aneurysmal subarachnoid hemorrhage (aSAH) is a neurological emergency which is associated with a high risk of mortality and permanent disability. Subarachnoid hemorrhages account for approximately 5–10% of all strokes; however, the case mortality rate of aSAH at 1 year is considerably higher (50%) when compared to ischemic stroke. Up to 10–15% of patients with aSAH die before reaching the hospital [1–7]. In addition to mortality, aSAH is associated with a substantial impairment in the quality of life, with significant neurological deficits and psychological sequelae. About one in five survivors of aSAH will not regain functional independence and only every fourth regains the same level of functionality as before the aSAH [1–6]. In worldwide estimates, when compared with ischemic strokes, aSAH patients are disproportionately younger, i.e., of working age with the age at insult mostly below 66 years. In Finland, the mean age of the event is as young as 55 years [8]. Subsequently, aSAH is associated with a considerable loss of independent functionality and responsible for the development of dependency early in life. Novel treatments are needed to mitigate the effects of aSAH both in the immediate aftermath (early brain injury, EBI) and thereafter to improve the current dismal outcomes.

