To explore the predictive value of the different MRI techniques (see details under the section of “Data collection and management”) alone and combined for clinical outcome at 3 months, and also at 1 and 2 years after SAH.To examine the pathophysiological pathways of the post-SAH period between the two treatment groups and to assess the predictive value of selected proteomics and metabolomics on severity of EBI and DCI and neurological outcome (i.e., good outcome: mRS 0–2 vs poor outcome: 3–6)To evaluate the role of microglial activation (see details under the section of “Data collection and management”) on the development of DCI.To explore the role of the cytokine level on the development of DCITo assess a combination of selected brain imaging markers obtained from different MRI techniques (see details under the section of “Data collection and management”), biomarkers (see secondary objectives # 8), plasma metabolomics (see details under the section of “Data collection and management”), CSF metabolomics and clinical examinations (e.g., motor score, pupillary light reflex with pupillometry, epileptic seizures) as a prognostication model for EBI, DCI, and neurological outcome at 3 months, at 1 and 2 years after SAH (i.e., good outcome: mRS 0–2 vs poor outcome: 3–6).To test the applicability of utilizing a brain network analysis with graph theoretical analysis and anatomical connectivity of white matter tracts (see details under the section of “Data collection and management”) in prognostic models for EBI, DCI, and neurological outcome at 3 months, at 1 and 2 years after SAH (i.e., good outcome: mRS 0–2 vs poor outcome: 3–6) and to investigate xenon’s effect on the connectivity.To unravel the mechanisms underpinning the development of EBI and DCI by utilizing brain imaging obtained from different MRI techniques (see details under the section of “Data collection and management”) and metabolomics (i.e., plasma and spinal fluid; see details under the section of “Data collection and Management”)To measure the clinical neurological outcome at 3 months and at 1 year and at 2 years.To develop a prognostication model for EBI and DCI and neurological outcome at 3 months and at 1 year and at 2 years after SAH

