### Trial design {8}

The Xe-SAH study is a prospective, multicenter phase II drug intervention trial. The study design is a single-blind, prospective superiority randomized two-armed parallel follow-up study. The primary objective of the study is to explore the potential neuroprotective effects of xenon, when administered within 6 h of the initial insult, in adult (≥ 18 years of age), mechanically ventilated aSAH patients with a Hunt-Hess grading of 3–5. There are two study arms: the control arm receiving the current standard of care while the intervention arm will be administered a 24-h xenon treatment in addition to the standard care.

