### Secondary outcome measures

Fractional anisotropy of white matter at cerebellum and/or at corpus callosum as assessed with the 1st MRI.Safety and tolerability of xenon, as assessed with a ratio of adverse events, serious adverse events, and suspected unexpected serious adverse reactions (SUSARSs) during the follow-up at 1 year between the xenon group and the control group.Composite of radiological EBI (within 72 h after the start of SAH symptoms), DCI, cerebral infarction (see definitions in detail under the section of secondary objectives) and poor outcome (good: mRS 0–2; poor: mRS 3–6) at 3-months and at 1 year.Neurogenic stress cardiomyopathy and stunned myocardium (i.e., myocardial injury caused by sympathetic storm and autonomic dysregulation with hs-troponin elevation, left ventricular dysfunction or ECG changes)ICP-level up to 14 days (i.e., as long as clinically relevant) after the onset of aSAH symptomsNeed for ICP therapies up to 14 days (i.e., as long as clinically relevant) after the onset of aSAH symptomsDuration of therapy for ICP control/monitoring up to 14 days (i.e., as long as clinically relevant) after the onset of aSAH symptomsPlasma catecholamine levelsDifference in selected biomarkers (NSE, NF-L, GFAB, S100B, UCH-L1, total-tau TNF-α, interleukins 6 and 10) and difference in metabolomic and lipidomic profiles in the blood and CSF between xenon and control group in predicting risk for EBI, vasospasm, DCI as well as a good neurological outcome at 3 months, 1 year, and at 2 years after the aSAH.Development of prognostication models with a selected combination of brain imaging and biomarkers obtained from various MRI techniques (see details under the section “Data collection and management”), clinical data, and metabolomics (see details under the section “Data collection and management”) by applying artificial intelligence and machine learning for EBI, vasospasm, DCI, and a good neurological outcome at 3 months, 1 year, and at 2 years after the aSAH.Difference in CTA, DSA, and MRI parameters obtained from various MRI techniques (see details under the section “Data collection and management”) between xenon and control group in predicting EBI, vasospasm, DCI, and a good neurological outcome at 3 months, 1 year, and at 2 years after the aSAH.Predictive value of computational fluid dynamics (CFD) (see details under the section “Data collection and management”) to detect the differences in the blood flow behavior in the recruited patients by applying 3D DSA to assess the risk of EBI within the first 72 h after the start of aSAH symptoms, vasospasm (within 21 days after the start of SAH symptoms) and DCI (between day 4 and 6 weeks after the start of SAH symptoms) and a good neurological outcome at 3 months, at 1 year, and at 2 years after the aSAH (mRS 0–2).Difference of metabolomics and lipidomics profiles of plasma and CSF between xenon and control group and in predicting the risk for EBI within the first 72 h after the start of aSAH symptoms, vasospasm (within 21 days after the start of SAH symptoms) and DCI (between day 4 and 6 weeks after the start of SAH symptoms) and a good neurological outcome at 3 months, at 1 year, and at 2 years after the aSAH (mRS 0-2).Difference of activity of microglial cells between the subjects in the xenon and control groups and in predicting the risk for DCI and a good neurological outcome at 3 months, 1 year, and at 2 years after the aSAH.

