The following MRI techniques will be used: (1) T2-weighted and fluid-attenuated inversion recovery (FLAIR) sequences; (2) T1-weighted 3D gradient echo sequence for volumetric analysis; (3) time of flight angiography (TOF) to visualize flow within vessels, without the need to administer a contrast agent; (4) brain perfusion imaging with dynamic susceptibility contrast (DSC), (5) a susceptibility-weighted imaging (SWI) sequence to image hemosiderin, (6) whole-brain (and region-of-interest level) white matter integrity from diffusion-weighted MRI data measured with diffusion tensor imaging (DTI; fractional anisotropy is the primary end-point of the current trial; (7) voxel-wise white matter microstructure from diffusion-weighted MRI data. A global voxel-wise data-driven Tract Based Spatial Statistics (TBSS) with DTI and other microstructural metrics will be applied; (8) constrained spherical deconvolution (CSD) technique will be used to estimate the orientation of multiple fiber populations, e.g., crossing fibers, in a voxel accurately and within a clinically feasible scan time. The fiber orientation distributions will be estimated with CSD and used to perform probabilistic fiber tractography for the whole brain and for certain tracts of interest. The whole brain tract networks will be analyzed with graph theoretical analysis [49–53].

In addition, all feasible patients (i.e., capable to co-operate adequately during the scan) will be scanned in the Turku PET Centre. The 1st scan will be performed 4 ±1 weeks after the onset of SAH symptoms with the 2nd scan being undertaken at 3 months after the onset of SAH symptoms. It will be explored whether [^11^C](R)-PK11195 can be used to test the hypothesis that xenon can exert a neuroprotective effect and to explore the role of inflammatory process in the extent of DCI and also the neurological outcome at 1 year after SAH. We postulate that this can be demonstrated by showing less signs of microglial activation in the xenon-treated group than in the reference therapy group and in the patients with good outcome, i.e., mRS 0–2 [54–56].

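### Microglial PET is limited to patients able to co-operate weeks after randomisation, so the between-arm difference describes co-operating survivors and is open to bias if xenon affects recovery

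*Protocol article*

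**What the plan says.** The rule for who is scanned is in the protocol article, section 18a (plans for assessment and collection of outcomes): "all feasible patients (i.e., capable to co-operate adequately during the scan) will be scanned in the Turku PET Centre". On timing, "The 1st scan will be performed 4 ±1 weeks after the onset of SAH symptoms", and a second scan follows at 3 months.

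The same section states the inference. Neuroprotection is to be shown by "less signs of microglial activation in the xenon-treated group than in the reference therapy group and in the patients with good outcome". The list of secondary outcome measures includes "Difference of activity of microglial cells between the subjects in the xenon and control groups", together with prediction of DCI and of good neurological outcome. Microglial activation also stands under the secondary objectives. The outcome split is "good outcome: mRS 0–2 vs poor outcome: 3–6", so death counts as poor outcome.

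The eligibility criteria admit intubated patients with GCS 3–12 and "Hunt-Hess grading of 3–5".

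The general analysis rules are in sections 20a and 20c. Analyses use whatever data are available and adjust for age, sex and site, with other baseline covariates where needed. The extent of missing data will be examined, chiefly for the primary outcome. The 30% loss allowed for under sample size concerns MRI only.

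**The concern.** Patients enrolled intubated with GCS 3–12 cannot be assumed able to co-operate in a scanner weeks later. Whether they can depends on surviving and recovering, which is what xenon is meant to improve. The condition for having a PET value is therefore a post-randomisation state close to the clinical outcome itself. It is a different gate from the one for MRI, which is done where imaging is safe.

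Two uses of the PET data are affected.

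- **Between-arm difference.** If xenon lets more of the severely injured reach the scanner, the xenon mean includes patients whose control counterparts are absent. A real reduction in activation would look smaller, and an effect on function alone could look like an increase in activation.
- **Link to outcome.** Patients who die before the scan, and those too impaired to co-operate, contribute nothing. The poor-outcome side of the comparison is left with its better members.

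The gate, the comparison and the inference are all fixed in this document. The general rules on available data and missing values do not recognise that a patient who died has no microglial value to recover.

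**Working it through.** **The plan's own figures.** No scan count, scan rate or power is given for PET. The only sample-size figure is for the MRI endpoint, and it reproduces: difference 0.02, SD 0.035, two-sided 0.05 and 80% power give 49 per arm by the normal formula and 50 per arm (100 in total) by the t-test. It matters here only because enrolment is set at 80 per arm, 160 in total.

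**Step 1: bias in the between-arm difference.** All inputs in this step except the 80 per arm are assumptions, because the document gives none.

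- Latent injury has correlation r = 0.3, 0.5 or 0.7 with microglial signal, and 0.8 with an index of inability to co-operate.
- A patient is scanned if that index lies below the cut-off giving the assumed share p.
- Xenon has no effect on microglia. It changes only the share scanned, from p0 (control) to p1 (xenon).

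With λ(p) = φ(Φ⁻¹(p))/p, the expected difference among scanned patients, xenon minus control, in SD units is

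bias = r × 0.8 × [λ(p0) − λ(p1)].

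The values are λ(0.3) = 1.159, λ(0.4) = 0.966, λ(0.5) = 0.798 and λ(0.6) = 0.644.

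| Control → xenon share scanned | r = 0.3 | r = 0.5 | r = 0.7 |
|---|---|---|---|
| 40% → 40% | 0 | 0 | 0 |
| 40% → 50% | +0.040 | +0.067 | +0.094 |
| 40% → 60% | +0.077 | +0.129 | +0.180 |
| 30% → 50% | +0.087 | +0.144 | +0.202 |

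Simulation of the same model (1 million per arm) agrees within 0.003; for 40% → 50% it gives 0.041, 0.067 and 0.095. Starting from 30%, a 10-point rise gives 0.046 to 0.108. A positive sign means apparently more activation under xenon. With a true benefit of 0.30 SD added to the 10- and 20-point scenarios, the simulated difference is between −0.26 and −0.10 SD.

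**Step 2: against sampling error.** With 80 per arm and 40% against 50% scanned, 32 and 40 patients have values. The standard error is √(1/32 + 1/40) = 0.24 SD. With 40% against 60% it is √(1/32 + 1/48) = 0.23 SD. The bias is below one standard error in every row of the table.

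**Step 3: effect of baseline adjustment.** Assume that baseline severity correlates 0.6 with later injury. Adding it as a covariate in the Step 1 model removes roughly a quarter of the bias, for example from 0.128 to 0.096 SD at r = 0.5 and 40% → 60%. It helps but does not cure the problem.

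**Step 4: poor-outcome patients who could be scanned.** The background gives 50% one-year mortality and 25–30% in-hospital mortality, and states: "About one in five survivors of aSAH will not regain functional independence". For 160 patients:

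- mortality 25%: 120 survivors, 120 × 0.2 = 24 dependent, 40 dead; 24/(24 + 40) = 38% of the poor-outcome group is alive;
- mortality 50%: 80 survivors, 80 × 0.2 = 16 dependent, 80 dead; 16/(16 + 80) = 17% is alive.

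If 25–50% of dependent survivors can co-operate (assumption), 4 to 12 of them are scanned. If 40–60% of survivors are dependent, as may be so in Hunt-Hess 3–5 (assumption), 8 to 36 are scanned, or 7–32% of the poor-outcome group. The range is wide because the inputs describe all aSAH and the co-operation rate is unknown.

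**The case against.** The strongest reply has five parts.

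- **Bias is not automatic.** A reader might infer that the PET comparison is biased as it stands. The document does not support that. With equal co-operation in the arms the bias is zero, and if xenon does nothing at all none is expected. This stands, and the point is worded conditionally.
- **The size may be small.** A reader might infer that a true effect is halved. That comes from a model in which xenon improves severity by 0.5 SD, which raises the scannable share by 16 to 18 points (for example 40% to 58%). The nearest figure in the document is the 6-month mortality in the earlier cardiac-arrest trial, 27.7% against 34.5%, about 7 points and in another disease. A 7-point rise gives a false increase of only about +0.06 SD in that model. This stands as a limit on size.
- **The share who can be scanned is not known.** A reader might compute 0.5 × 0.8 = 40% alive and independent and conclude that half or more can never be scanned. The 50% mortality is for all aSAH, and the background notes up to 10–15% dying before hospital, who could not be enrolled. The severity criteria pull the other way. Nor does the document equate co-operating in a scanner with mRS 0–2; some patients with mRS 3 could be scanned. So the claim that most of the poor-outcome group is removed is not established.
- **The endpoint is minor.** It is secondary, late in a long list, and introduced as something to be explored. True, but the same section then says what result would demonstrate the effect.
- **Details may sit in the SAP.** Missing-data rules and tables often do, and covariates beyond age, sex and site are already permitted. The selection rule and the inference drawn from it, however, are written here.

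**Conclusion.** The concern holds in conditional form. The protocol restricts PET to co-operating survivors and then reads the between-arm difference as a test of neuroprotection. That comparison loses the protection of randomisation exactly when xenon affects survival or recovery, which is the trial's own hypothesis.

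Under the assumed models the bias runs against xenon: about +0.04 to +0.10 SD for a rise in co-operation from 40% to 50%, and +0.08 to +0.20 SD for 20 points. These sizes rest on assumed correlations and scan rates, and the document fixes neither size nor sign. The risk is of understating a benefit or showing a spurious increase, rather than of a large false positive.

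The association of PET with mRS 0–2 against 3–6 is estimated in a truncated poor-outcome group. How small that group will be cannot be settled from the document.

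This should be changed but does not threaten the trial. The endpoint is secondary and exploratory in intent, and the primary fractional anisotropy endpoint is outside this point.

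**What to change.** 1. In the secondary outcome list and in section 18a, state that the PET comparison applies to survivors able to co-operate and is not by itself evidence of neuroprotection.
2. Pre-specify adjustment of the scanned-only comparison for baseline Hunt-Hess grade and GCS as well as age, sex and site, rather than leaving it to need.
3. Report scanned and unscanned patients by arm at each scan time, with reasons (died, unable to co-operate, other).
4. Add one sensitivity analysis for selection: bounds for patients who would be scannable in either arm, or inverse-probability weighting from baseline data.

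A worst-rank test that places the dead and unscannable below everyone else is not advised. It keeps all randomised patients, but with many tied at the bottom it would mostly re-test death and disability, which mRS already captures, and could suggest a microglial effect where there is none.

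The cost is a weaker claim from the PET data and a little more analysis. No extra scans are needed.

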### Plans to promote participant retention and complete follow-up {18b}

Only routine encouragement if necessary.

### Data management {19}

Data collected upon arrival and all neuroradiology findings will be stored in an electronic web-based study database (Redcap, https://www.project-redcap.org/ [62, 63]). This data will be securely stored at the servers of the corresponding city’s universities where the patients are being treated. Intensive care data, including blood pressure, blood samples, and ICP data for example will be stored at a secure server at the corresponding University Hospitals in accordance with hospital guidelines and the Data Management Plan as described below in this protocol.

Access to clinical data with patient IDs is strictly limited to the clinicians treating the patients and maintaining the database. Exports of the clinical data for analyses are always pseudononymized to protect patient confidentiality. The imaging data exports are stored only at MRI unit and Turku PET Centre of Turku University Hospital, which are audited workspace environments that is designed to host sensitive data for collaboration. All researchers sign a non-confidentiality agreement with strict rules on data handling before they are granted access to the exports. The study sites have ethical review board approvals for collection and working with clinical material and data.

All data with direct or indirect identification information will be stored in encrypted form and a separately stored decryption code will be stored with access by the PI. Essential documents shall be archived safely and securely.

Each study patient is identified by a patient code (i.e., first two initials of first and last name and subject number). The patient identity (initials and screening/subject number, the subject’s first name, last name, date of birth, social security number) is recorded on a separate register (i.e., patient identity file) which can be accessed only by the PI with a password. Study subject records, subject screening log, all original signed informed consent forms, and CRFs will be kept in the Investigator’s study file to enable the follow-up assessments by safety committee and monitor. Investigator’s study file can be accessed only by the PI and biostatistician with a password.

The study subject code (initials and screening/subject number), date of informed consent, date of entry or date of exclusion, and the reason for exclusion for those recruited for screening but not fulfilling the inclusion criteria and therefore excluded will be recorded in the subject screening log.

### Confidentiality {27}

Data is stored in accordance with local data protection guidelines applying the data management plan as described in the protocol; see the section “Data collection and management”.

### Plans for collection, laboratory evaluation, and storage of biological specimens for genetic or molecular analysis in this trial/future use {33}

Biochemical assessment: A blood sample of 20 ml for determination of plasma catecholamines, plasma metabolomics (see details of metabolomics under the section “Data collection and management”), cardiac enzyme release (P-hs-troponin-T and heart fatty-acid binding protein), neuron-specific enolase (NSE), neurofilament light (NF-L), glial fibrillary acidic protein (GFAP), calcium-binding protein S100B (S100B), ubiquitin carboxyterminal hydrolase L1 (UCH-L1), total tau, and cytokines (tumor necrosis factor alpha, interleukins 6 and 10) will be analyzed at ICU arrival and at 24h, at 48h, and at 72h after onset of SAH symptoms; urine catecholamines during first and second 24 h. In addition, a sample of spinal fluid will be collected through EVD at ICU arrival or as soon as it is in place and at 24h, at 48h, and at 72h after onset of SAH symptoms for assessment of metabolomics. P-hsTn-T and P-NSE will be determined by a local university hospital laboratory with standard methods. The samples will be destroyed 10 years after completion of the study. In addition, the patient has a right to require destruction of the samples at any time. In this study, no tissue samples will be collected, and no genetic analysis are conducted.

## Statistical methods

### Statistical methods for primary and secondary outcomes {20a}

The primary outcome measure is a global fractional anisotropy of white matter of diffusion tensor imaging (DTI) as assessed in the 1st MRI. The univariate distributions of variables and the associations between variables will be described using summary statistics. Basic statistical tests (two-sample *t*-test, Mann-Whitney *U*-test, chi-square test, and Fisher exact test) will be used in the preliminary analysis to compare the xenon-treated and control groups. Kaplan-Meier curves and Cox regression analyses will be applied when examining the occurrence of end-point events. An analysis of variance of repeated measurements will be applied for normally distributed outcome variables. In the case of other types of variables, the analysis will be based on generalized linear mixed models which include comprehensive and general tools to analyze longitudinal data. General linear model for normally distributed outcomes and generalized linear models for other types of variables will be used for analyzing data at different time points. The analyses will be adjusted for age, sex, and site, and other baseline characteristics of patients will be used as covariates when needed. The adjusted analysis will be considered to be the main analysis. The statistical analysis will be based on all available data. If an analysis is based only on complete cases, it will be mentioned separately. The data will be analyzed according to intention-to-treat and per-protocol populations. The differences will be presented as mean differences with 95% confidence intervals for continuous outcomes, odds ratios with 95% confidence intervals for categorical outcomes, and hazard ratios with 95% confidence intervals in survival analyses. A two-sided statistical test with a significance level of 0.05 will be used in the statistical analyses.

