Even after successful microsurgical or endovascular treatment of the ruptured aneurysm, DCI is still a potentially devastating clinical syndrome related to aSAH and it is the most significant cause for morbidity and mortality in patients who survive the initial aSAH [1–3, 12]. DCI is a clinical syndrome of focal neurological and cognitive deficits presenting in about 30% of aSAH patients at 3–14 days after the initial insult, which might progress to infarction [1–5, 12]. While an angiographically evident vasospasm in the cerebral arteries can be detected in 70% of patients, less than half of them develop any symptoms or ischemia in the territory supplied by the narrowed artery [1]. In addition, treatment with the calcium-channel blocker, nimodipine, which is currently the standard of care and the only pharmacological intervention that has been shown to reduce the risk of DCI and improve neurologic outcome by one-third after aSAH, does not alter the incidence or severity of delayed cerebral artery vasospasm [13]. Furthermore, other clinical trials involving drugs that exert a significant impact on vasospasm did not have any impact on the risk of DCI or outcomes [1, 12, 14]. Consequently, recent research has questioned whether there is truly a direct causal relationship between cerebral vasospasm and DCI and it has been suggested that DCI following an aSAH is actually the result of a variety of different pathophysiological mechanisms, which are currently incompletely understood [1, 12, 15, 16]. From preclinical and clinical studies, a number of possible mechanisms other than vasospasm to explain the link between DCI and infarction have been proposed including microthromboembolism, cortical spreading depolarization and ischemia, microcirculatory dysfunction, inflammation, and impaired cerebral autoregulation [12]. It has been recommended that the main outcomes of clinical trials investigating strategies to prevent DCI should measure the extent of cerebral infarction by either radiologic imaging or autopsy biopsy as well as the patient’s functional outcome [17].

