
In 2016, we reported (Xe-HYPOTHECA trial; Clinicaltrials.gov NCT00879892) that xenon was able to attenuate the white matter injury after global ischemia after cardiac arrest [43]. The effect was mainly due to less extensive myelin damage in the xenon-treated group than in the control group. This was demonstrated by a significantly higher global fractional anisotropy of diffusion tensor imaging of white matter tracts in the xenon-treated patients than in the control patients [43]. The proper function of white matter is fundamental for good neurocognitive performance. Nonetheless, the Xe-HypotheCA trial was not powered to assess the clinical outcome. For example, the 6-month mortality was 15/55 (27.7 %) in the xenon-treated group and 19/55 (34.5 %) in the control group (adjusted HR 0.49 [95% CI 0.23–1.01], *P*=0.053). The interpretation of the authors was that this result was due to a combination of xenon’s neuro-and cardioprotective properties, which may also be clinically beneficial after aSAH.

Despite improvements in medical technology and advances in medical science, aSAH mortality and disability rates have remained virtually the same during the past 10 years [7]. The age and illness severity adjusted in-hospital mortality of 25–30% has also not changed over a span of 12 years, from 2003 to 2015 [5, 6]. Therefore, it is clear that new neuroprotective strategies are needed to attenuate the early and delayed brain injury occurring after an aSAH in order to improve the current dismal situation.

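### If the unnamed end-point events include DCI, infarction or vasospasm, Kaplan-Meier curves overstate their incidence; ICP-therapy duration and repeated-measures ANOVA have related weaknesses over death and missing samples

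*Protocol article*

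**What the plan says.** Under Statistical methods for primary and secondary outcomes {20a}, the article says "Kaplan-Meier curves and Cox regression analyses will be applied when examining the occurrence of end-point events", with results given as "hazard ratios with 95% confidence intervals in survival analyses". It does not say which events are meant. Categorical results are to be given as "odds ratios with 95% confidence intervals for categorical outcomes". The same paragraph says "An analysis of variance of repeated measurements will be applied for normally distributed outcome variables" and assigns generalized linear mixed models to other types of variable. It then adds "The statistical analysis will be based on all available data" and "If an analysis is based only on complete cases, it will be mentioned separately".

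The outcomes concerned are in Objectives {7} and Secondary outcome measures. Infarction and DCI are counted from day 4 to week 6, and vasospasm over 21 days. The length of ICP-directed therapy or monitoring, to day 14 at most, is an outcome of its own, with no rule for patients who die in that time. All-cause mortality is not listed separately; death enters through mRS 6, which is part of the composite with EBI, DCI and infarction. The specimen section {33} has blood biomarkers sampled at ICU arrival and at 24, 48 and 72 h.

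On frequency, Background and rationale {6a} describes DCI as "presenting in about 30% of aSAH patients at 3–14 days after the initial insult" and puts "age and illness severity adjusted in-hospital mortality" at 25–30%.

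**The concern.** Three of the stated choices depend on what happens to patients who die early or miss a sample.

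- **Event curves.** Kaplan-Meier treats a censored patient as still able to have the event later. A patient who has died cannot develop DCI. One minus Kaplan-Meier with deaths censored therefore estimates the incidence in a setting where nobody dies, and it is higher than the proportion of patients who actually have the event.
- **ICP-therapy duration.** A patient who dies on day 2 contributes at most two days. Fewer days reads as a better result, so early death counts in an arm's favour.
- **Repeated measures.** In its classical form, repeated-measures ANOVA needs every time point for every patient. A patient with one missing sample is left out entirely, although the paragraph promises to use all available data.

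At stake are the absolute event rates that would be reported for DCI and infarction, the direction of the ICP-therapy comparison, and the number of patients kept in the biomarker analyses.

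**Working it through.** The plan gives no figure of its own on this point, so there is none to reproduce. The checks below show how large each effect could be.

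**1. Kaplan-Meier with deaths censored**

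Inputs: DCI incidence F = 0.30 (Background). The share d who die before DCI is not given, so it is varied from 5% to 30%. The upper end borrows the 25–30% in-hospital mortality, which covers deaths at any time in hospital and aSAH patients in general.

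With constant hazards:
- total cumulative hazard H = −ln(1 − F − d)
- DCI part H₁ = H × F / (F + d)
- Kaplan-Meier reading = 1 − exp(−H₁)

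For d = 0.25: H = −ln(0.45) = 0.7985; H₁ = 0.7985 × 0.30/0.55 = 0.4355; reading = 1 − exp(−0.4355) = 35.3%.

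If all these deaths precede any DCI, the reading is F/(1 − d). For d = 0.25 it is 0.30/0.75 = 40.0%.

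| Die before DCI (assumed) | Constant hazards | All deaths first | Cumulative incidence |
|---|---|---|---|
| 5% | 30.9% | 31.6% | 30% |
| 10% | 31.8% | 33.3% | 30% |
| 15% | 32.9% | 35.3% | 30% |
| 20% | 34.0% | 37.5% | 30% |
| 25% | 35.3% | 40.0% | 30% |
| 30% | 36.8% | 42.9% | 30% |

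**2. Does this distort the comparison between arms?**

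Take d = 0.25 in the control arm. The death hazard is 0.7985 − 0.4355 = 0.3630. Suppose xenon leaves the DCI hazard alone and multiplies the death hazard by 0.49, the adjusted mortality hazard ratio that the Background quotes from the cardiac-arrest trial (95% CI 0.23–1.01). The xenon death hazard is 0.1779 and the total hazard is 0.6134.

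- Kaplan-Meier with deaths censored: 35.3% in both arms.
- Cox with deaths censored: hazard ratio 1.0.
- Cumulative incidence of DCI: 30.0% in control; in xenon 0.4355/0.6134 × (1 − exp(−0.6134)) = 32.6%.
- DCI or death: 55.0% in control; 1 − exp(−0.6134) = 45.8% in xenon.

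In this scenario the Kaplan-Meier level is too high, but equally so in both arms, and Cox shows no difference.

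**3. ICP-therapy duration**

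Illustration with assumed values: 10 days in survivors, 2 days in early deaths.

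- Arm with 30% early death: 0.30 × 2 + 0.70 × 10 = 7.6 days.
- Arm with 20% early death: 0.20 × 2 + 0.80 × 10 = 8.4 days.

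The arm with more deaths looks 0.8 day better, although survivors need the same therapy in both arms.

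**4. Repeated-measures ANOVA**

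The article gives no rate of missing samples. If 10% were missing at each of the three samples after ICU arrival, complete cases would be 0.9³ = 72.9% with independent gaps, but 90% if the same patients were missing each time. The loss depends on the pattern and cannot be fixed from the document.

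**The case against.** The strongest reply is that the target is not stated. The methods paragraph never assigns Kaplan-Meier or Cox to DCI, infarction or vasospasm. Binary outcomes may be reported as odds ratios, and vasospasm appears among the outcomes only as something to be predicted. The composite counts death through mRS 6, so it does not reward early death. Which event gets which method may be settled in an analysis plan that is not shown. This stands, and it makes the first part conditional. It does not remove it: mortality is not listed as an outcome, while non-fatal events with time windows are.

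A reader might infer that, if xenon lowers mortality, the planned Kaplan-Meier and Cox analyses would show false harm on DCI. The documents do not support that. In the scenario above both show no difference. A Cox model with deaths censored estimates the cause-specific hazard ratio, which is a valid quantity. The rise from 30.0% to 32.6% belongs to the cumulative incidence and reflects more patients living long enough to be at risk. It has to be read beside event-or-death, which falls.

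A reader might also take 25% as the share dying before DCI. The article gives no such figure. The 25–30% is total in-hospital mortality for aSAH generally, not for intubated Hunt-Hess 3–5 patients, and some of those deaths follow DCI. At 5–10% the excess is only about 1–3 points.

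On ANOVA, listwise deletion is a property of the classical method and is not announced as a plan. The paragraph foresees complete-case analyses and promises to flag them. The two statements are therefore in tension, not in outright contradiction.

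**Conclusion.** The point holds in a limited form.

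- **Curves.** If the end-point events include the listed non-fatal ones, Kaplan-Meier with deaths censored overstates their incidence. For a true DCI incidence of 30%, the excess under constant hazards is about 1–2 points if 5–10% die first and 5–7 points if 25–30% do. If all those deaths precede DCI, it is about 2–3 and 10–13 points. The share dying first is an assumption throughout. The Cox cause-specific hazard ratio is not at fault.
- **ICP-therapy duration.** As listed, it can favour the arm with more early deaths. This follows from the definition; the 0.8 day is only an illustration.
- **Repeated-measures ANOVA.** In its classical form it does not fit the commitment to all available data. How many patients would be lost is unknown.

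All three concern secondary outcomes. The primary outcome, global fractional anisotropy at the first MRI, is not touched by this point. The changes should be made, but the trial's main conclusion does not depend on them.

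**What to change.** 1. Name the end-point events. For DCI, infarction and any time-to-event analysis of vasospasm, show cumulative incidence curves (Aalen-Johansen) with death as a competing event. Report the cause-specific hazard ratio together with the hazard ratio for event-or-death. Keep Kaplan-Meier for mortality and for composites that include death.
2. Analyse ICP therapy with a measure that counts death as unfavourable, for example days alive and free of ICP therapy to day 14 with death ranked worst. Report the raw duration beside it.
3. Replace repeated-measures ANOVA with a likelihood-based linear mixed model. This uses every available sample and matches the generalized linear mixed models already planned for other variables.

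The cost is wording in the protocol or analysis plan and slightly more analysis; no new data are needed. The one drawback is that the ICP measure then mixes death with length of therapy, which is why the raw duration should stay alongside it.
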